#### Secondary Outcomes

A significant increase in serum levels of telomerase activity (baseline and postintervention), indicated by a *P* value <.05, along with a moderate to large Cohen *d* value suggesting a meaningful change will be interpreted as evidence of the regenerative impact of the protocol. Higher telomerase activity is linked to increased cellular lifespan and delayed biological aging.

### Data Collection Instruments: Technical Specifications, Reliability, and Validity

Data collection is performed using standardized, high-performance commercial biochemical assays and laboratory instruments. The specific instruments, along with their established analytical reliability and validity profiles, are detailed in the following sections.

#### MDA Assay

Serum MDA is quantified as an index of lipid peroxidation using a high-sensitivity Colorimetric Assay Kit (E-BC-K025-S [16]; using the thiobarbituric acid reactive substances method). Absorbance is measured at 532 nm using a calibrated multimode microplate spectrophotometer reader. The assay exhibits high analytical validity with a linear detection range spanning from 0.1 nmol/mL to 100 nmol/mL and is sensitive to analyze 0.38 nmol/mL. The instrument setup maintains an intra-assay coefficient of variation (CV) of 4.9% and an interassay CV of 8.0%, ensuring excellent analytical reproducibility across separate experimental runs.

#### Total SOD Activity Assay

Serum total SOD (T-SOD) activity is quantitatively measured using a standardized Elabscience T-SOD Activity Assay Kit (hydroxylamine method, catalog number: E-BC-K019-S) [17]. Absorbance is measured at 550 nm using a calibrated spectrophotometer instrument. The assay uses a xanthine and xanthine oxidase reaction system to generate superoxide anion free radicals that oxidize hydroxylamine to form nitrite. Nitrite reacts with a developer to form a purplish-red compound. Endogenous T-SOD in the serum specifically intercepts and disproportionates the superoxide radicals, inhibiting nitrite formation. The resulting reduction in absorbance is perfectly, negatively correlated with serum T-SOD activity, ensuring high analytical validity and specificity for biological SOD isoforms.

#### Analytical Ranges

The instrument setup delivers a certified sensitivity limit of 4.7 U/mL and maintains a broad, clinically validated linear detection range of 4.7‐166 U/mL.

#### Reliability (Precision)

The kit protocol uses internal controls, double-distilled water blanks, and strict room-temperature equilibration routines to guarantee reproducibility. Run reliability is reinforced by performing sample evaluations in duplicate to maintain a strict intra-assay precision CV threshold of 2.8% and an inter-assay precision CV of 6.3%.

#### Telomerase Activity Assay

Quantitative determination of human telomerase concentration is executed using a standardized commercial Elabscience Human TE ELISA Kit (sandwich-ELISA method, catalog number: E-EL-H0164) [18]. Optical density is measured spectrophotometrically at a wavelength of λ=450 nm±2 nm using a calibrated microplate reader. The instrument setup uses a precoated microplate with an antibody specific to human telomerase. Following sample incubation, a biotinylated detection antibody specific for human telomerase is added. Substrate reaction is colorimetrically recorded via progressive blue-to-yellow conversion following the addition of an acidic stop solution. The method provides excellent analytical validity with zero cross-reactivity or interference from structural analogs. The instrument setup features an exact analytical sensitivity limit of 0.1 ng/mL

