**Methods:**

The study was prospectively registered in the Clinical Trial Registry-India (CTRI; CTRI/2024/02/062176), uses a pre-posttest study design, and includes 53 participants 35 years to 65 years old. The study is exploratory and lacks a control group. Those with a BMI between 18.5 kg/m^2^ and 25 kg/m^2^, with stable weight for 3 months immediately prior to the study, with *madhyama koshta* (medium nature of bowel evacuation, as assessed using aquestionnaire), who are *Vamanarha* (eligible for therapeutic emesis) and *Virechanarha* (eligible for therapeutic purgation), and who do not meet the exclusion criteria will be included in the study. The interventions include emesis in the spring and purgation in the autumn season, preceded by *Snehana* (oleation) and *Swedana* (fomentation) and followed by the *Samsarjana karma* (specialized menu of diets) depending on the measurement of purification. Trial duration will range from 18 days to 20 days for each participant, and the total study duration will be 3 years. The serum levels of MDA, SOD, and telomerase activity will be measured on day 0 and on the next day following completion of the *Samsarjana karma* (18th-20th day). Continuous variables for primary biological endpoints including serum MDA, T-SOD, and telomerase activity will be evaluated using paired-samples *t* tests or Wilcoxon signed-rank tests, with potential missing data managed under a missing completely at random assumption using available case analysis (pairwise deletion) cross-verified by a conservative baseline observation carried forward (BOCF) sensitivity test. The effect size will be also determined.

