#### Secondary Objective

The secondary objective is to determine the change in serum telomerase activity from baseline to postintervention.

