#### Primary Variables (Endpoints)

The endpoints consist of continuous laboratory biomarker change scores measuring oxidative stress indicators, specifically MDA and SOD, and cellular longevity parameters, including telomerase activity.

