### Statistical Measures

The change in values of the outcome measures including MDA, SOD, telomerase activity, and telomere length will be recorded. The data will be tested for normality using the Shapiro-Wilk test. They will be tested for significance using paired *t* tests (if the data are normally distributed) or the Wilcoxon Signed Rank test (if the data are not normally distributed). A *P* value <.05 will be considered significant. All statistical analysis will be conducted using SPSS version 31 (IBM Corp). Moreover, a secondary exploratory subgroup analysis will be conducted within and between the 2 cohorts (*Vamana* and *Virechana* groups) based on the distribution of the data. If the data are normally distributed, within-group analysis will be conducted using paired *t* tests and between-group analysis will be conducted with *t* tests, whereas Wilcoxon Sign Ranked tests and Mann-Whitney *U* tests will be used, respectively, for data that are not normally distributed.

Cohen *d* effect sizes will also be calculated to address the exploratory nature of the study and evaluate the clinical and biological relevance of changes in biomarkers (ie, MDA, SOD, and telomerase activity). Results will be interpreted based on the magnitude and directionality of these effect sizes (small: 0.2; medium: 0.5; large: 0.8) to provide a standardized measure of treatment impact beyond simple *P* value testing.

Given the exploratory, hypothesis-generating design of this pilot study, secondary multivariable analyses will be introduced to evaluate the influence of potential baseline confounders. For normally distributed continuous data, an analysis of covariance (ANCOVA) will compare postintervention outcomes between the 2 seasonal subcohorts (*Vamana* vs *Virechana*) using individual pre-intervention scores as the baseline covariate to mathematically adjust for initial biological variation. Additionally, to evaluate the entire cohort of 53 participants as a unified group, multiple linear regression models will be constructed using the postintervention scores as the dependent variable, entering baseline biomarker values, age, sex, and baseline BMI as independent predictors to systematically control for demographic and physical confounding variables.

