## Discussion

### Theories Underpinning the Study

*Ritu sodhana* or seasonal purification is generally intended to eliminate the seasonal accumulation of humors. This process thereby reduces the susceptibility of seasonal disorders [14]. Acharya Charaka in the context of *Ritu sodhana* has put forth an additional statement that administration of seasonal biopurification will bestow rejuvenation and improve health span [19]. Even though these procedures have been evaluated for their clinical efficacies, its influence on biomarkers for aging has not yet been evaluated. This gap underpins the development of this research protocol, which aims to generate preliminary evidence for this purpose.

*Trikatu Churna,* used for *pachana* and *deepana*, has bioactive constituents including piperine, gingerols, and shogaols and has demonstrated effects on gastric secretion, gut motility, enzymatic activity, splanchnic circulation, and nutrient bioavailability, supporting improved digestive efficiency and systemic absorption [20,21]. This serves as metabolic priming, which is essential to ensure effective digestion and absorption prior to the administration of ghee. *Moorchita ghruta* [22] is widely used in clinical practice. Since the cohort includes healthy volunteers, no other medicated ghee was chosen. *Moorchita taila* [23] was chosen for external application owing to its popularity for the panchakarma procedure. *Trivrut lehya* is used for *Virechanakarma* with limited complications [24].

Based on this framework, we expect that *sodhana* will aid with releasing the waste metabolites, thereby influencing the values of MDA, SOD, and telomerase activity to trigger measurable anti-aging pathway responses across our cohort of 53 healthy volunteers. The hypothesized primary findings include a statistically significant pre-to-postintervention drop in oxidative tissue damage evidenced by a reduction in MDA levels coupled with a significant upregulation of cellular antioxidant defenses, marked by enhanced SOD activity. Furthermore, it is anticipated that this intensive detoxification phase will positively modulate cellular longevity clocks, manifesting as stabilized or elevated telomerase activity, thereby providing an objective, molecular validation of Acharya Charaka’s classical rejuvenation hypothesis.

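### The telomerase endpoint is named, ranked and interpreted as enzyme activity, but the assay described measures serum concentration, so the regeneration and longevity inferences are not supported

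*Protocol article*

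**What the plan says.** **What is measured.** Under Telomerase Activity Assay: "Quantitative determination of human telomerase concentration is executed using a standardized commercial Elabscience Human TE ELISA Kit". The principle is antibody capture: "The instrument setup uses a precoated microplate with an antibody specific to human telomerase", followed by a biotinylated detection antibody and an optical density reading at 450 nm. The detection range under the Analytical Ranges heading that follows is 0.16 to 10 ng/mL. Data Collection Form Accessibility lists telomerase concentrations among the fields of the case report form.

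**What is named.** Secondary Objective: "The secondary objective is to determine the change in serum telomerase activity from baseline to postintervention". The same label, activity, is used in the abstract, Primary Variables (Endpoints), Secondary Outcomes, Core Outcome Set and Summary Measures, Statistical Measures, Theories Underpinning the Study and Limitations.

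**How it is to be read.** Secondary Outcomes asks for a significant increase (P<.05) with a moderate to large Cohen d, takes that as a sign of a regenerative effect, and adds: "Higher telomerase activity is linked to increased cellular lifespan and delayed biological aging". Theories Underpinning the Study anticipates a benefit "manifesting as stabilized or elevated telomerase activity" and treats this as molecular confirmation of the classical rejuvenation hypothesis. Limitations concedes that MDA and T-SOD are short-term surrogates and presents telomerase as the answer to that limitation.

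**How it is ranked.** It is secondary in Secondary Objective and Secondary Outcomes. It is primary in the abstract's Methods, "Continuous variables for primary biological endpoints including serum MDA, T-SOD, and telomerase activity will be evaluated", and in the estimand's Primary Variables, "specifically MDA and SOD, and cellular longevity parameters, including telomerase activity".

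**What remains of telomere length.** Modifications reports its removal with ethics approval. Statistical Measures still says that "MDA, SOD, telomerase activity, and telomere length will be recorded", and the closing paragraph of the Limitations section still promises data on it.

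**The concern.** How much of an enzyme protein is present and how fast that enzyme works are different quantities. If the plan is followed as written, the report will test a concentration, call it activity, and attach to it an interpretation written for activity.

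This matters more here than a loose label usually would, because telomerase carries the ageing argument. The protocol accepts that MDA and T-SOD do not show delayed ageing and relies on telomerase to go further. The caveat given for those two markers is not extended to it.

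Two further inconsistencies make the result harder to judge. The rank of the endpoint differs between sections. The Discussion also describes a favourable outcome more loosely than the outcome section does. A reader holding the final report against this article could find support for either version.

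**Working it through.** The point does not rest on a figure in the plan, so the check is a comparison of its statements.

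**1. Assay against label.**

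| Source | Quantity |
|---|---|
| Telomerase Activity Assay, text | Human telomerase concentration by sandwich ELISA |
| Analytical Ranges (telomerase) | ng/mL, a mass concentration |
| Data Collection Form Accessibility | Telomerase concentrations |
| Secondary Objective, Secondary Outcomes, Statistical Measures and others | Telomerase activity |

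The article supplies its own contrast. Total SOD Activity Assay describes an enzymatic reaction in which the sample's SOD intercepts superoxide, and results are in U/mL. That is an activity measurement. Nothing comparable is described for telomerase. The colour reaction in the telomerase section follows addition of the detection antibody and is the read-out of the ELISA; it does not show telomerase acting on its own substrate.

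**2. Inference against measurement.** The chain in Secondary Outcomes and Limitations runs from a rise in activity, to regeneration and longer cellular lifespan, to a marker that goes beyond short-term redox change. The first link is missing, because activity is not measured. The design adds a second gap: there is one group and no untreated comparator, as Limitations states, so a change from baseline cannot be separated from other influences over the 18 to 20 days.

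**3. Rank.**

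| Section | Rank of telomerase |
|---|---|
| Primary Objective, Trial Design, Primary Outcome | Not included (MDA and SOD only) |
| Secondary Objective, Secondary Outcomes | Secondary |
| Abstract, Methods | Primary |
| Primary Variables (Endpoints), within a single primary estimand | Primary |

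The objectives, design and outcome sections agree with one another. The abstract and the estimand are the outliers.

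**4. What counts as a favourable result.** Secondary Outcomes sets three conditions: an increase, P<.05, and a moderate to large Cohen d. An unchanged level meets none of them. Theories Underpinning the Study would nevertheless accept a stabilised level as confirmation. Stabilised is not defined. Without a control group, a flat level cannot show that a decline was prevented, because the course without treatment is unknown.

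**5. Telomere length.** Modifications removes it. Statistical Measures and the closing paragraph of Limitations keep it. Both are current text, so this is a residue to delete.

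**The case against.** **The study is exploratory.** The article calls itself hypothesis-generating, its abstract conclusion does not mention telomerase, and its objectives and outcome sections consistently make telomerase secondary. That stands, and it limits the damage. It does not repair the label, and Limitations still gives telomerase the role of a deeper longevity marker.

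**The rank is open to choice after the data are seen.** A reader might infer this. The documents do not go that far: five sections agree on the rank and two differ. The registry record is not shown, so it cannot be said what is fixed there.

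**A third primary endpoint inflates the false-positive rate.** A reader might compute, for independent tests at an unadjusted two-sided .05, 1 − 0.95² = 9.75% for two endpoints and 1 − 0.95³ = 14.3% for three. This is not the protocol's success rule, which also requires a stated direction and a moderate to large Cohen d:

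- Direction alone: 1 − 0.975² = 4.9% and 1 − 0.975³ = 7.3%.
- Direction plus d ≥ 0.5 (taking the protocol's medium value as the threshold, n = 53): t = 0.5 × √53 = 3.64, one-sided p = 0.00031, giving about 0.06% and 0.09%.

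The inflation figure should not be used. The inconsistency in rank stands without it.

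**A null result formally counts as success.** A reader might take the Discussion to mean this and put the chance of a favourable reading under no effect at 97.5%. That figure equates stabilised with no significant fall, a definition the documents do not give. The wording describes an expectation in the Discussion and does not replace the rule in Secondary Outcomes. What stands is a conflict between the two passages.

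**Conclusion.** Wrong as written. On the article's own description, the telomerase assay yields a serum concentration in ng/mL, while the endpoint is named, tested and interpreted as activity. Change in concentration can be reported. The inferences to regeneration, lifespan and a deeper longevity marker cannot be drawn from it, and the single-group design weakens them further.

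The inconsistent rank, the looser Discussion wording and the leftover telomere length are real contradictions, but lesser ones. The whole point concerns one of three biomarkers. Its size lies in what the trial may claim; no error rate or loss of power is asserted. The verdict assumes that the assay section describes the kit actually used and that no separate activity assay exists, since none is mentioned.

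**What to change.** 1. Name the endpoint *serum telomerase concentration (ELISA, ng/mL)* wherever the trial's own measurement is meant, including the abstract, Secondary Objective, Primary Variables (Endpoints), the assay heading, Secondary Outcomes, Core Outcome Set and Summary Measures, Statistical Measures, Theories Underpinning the Study and Limitations. Background statements about telomerase biology, or about studies that measured activity, can stay.
2. Remove the inferences to activity, regeneration, lifespan and longevity in Secondary Outcomes, Core Outcome Set and Summary Measures, Theories Underpinning the Study and Limitations. Extend the surrogate caveat for MDA and T-SOD to this marker.
3. Make it secondary in the abstract's Methods and in the estimand, to match the objectives and outcomes.
4. In Theories Underpinning the Study, drop the reference to a stabilised level so that the text matches the rule in Secondary Outcomes.
5. Delete telomere length from Statistical Measures and from the closing paragraph of Limitations, as Modifications already decided.

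The cost is editorial, plus aligning the registry entry if it carries the same label. No new assay, samples or participants are needed. The downside is a more modest claim for this marker. The article says that data analysis is pending, so the changes are best made and dated before results are seen.

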#### Analytical Ranges

The assay delivers an exact sensitivity limit of 0.09 ng/mL and tracks a linear detection range of 0.16‐10 ng/mL.

### Data Quality Assurance Processes

To safeguard the accuracy and integrity of the clinical dataset, data quality is strictly managed through triplicate testing and blinded sample coding. To eliminate analytical errors, serum samples for MDA, T-SOD, and human telomerase are analyzed strictly in triplicate wells, with an automatic re-assay protocol enforced if the variance between duplicates exceeds a CV of 10%. Furthermore, all specimen tubes are stripped of identifiers and masked with unique alphanumeric codes, ensuring that laboratory personnel remain completely blinded to participant identities and trial time points throughout the assay phase.

### Data Collection Personnel and Process

The collection of samples is done at the hospital laboratory by trained lab technicians. The biochemical analysis is done by a trained personnel at the Amrita Centre for Advanced Research in Ayurveda lab to generate the values of MDA, SOD, and telomerase activity. The principal investigator collects the report and records them in the CRF. No data collection is performed by participants, caregivers, or nonclinical personnel.

### Core Outcome Set and Summary Measures

Currently, no standardized core outcome set has been developed or registered for the evaluation of Panchakarma procedures (such as *Snehapana, Vamana*, and *Virechana*) in healthy volunteer populations. Consequently, the biomarkers chosen for this exploratory study—MDA, SOD, and telomerase activity—were selected independently based on cellular aging and oxidative stress hypotheses.

The continuous marker of lipid peroxidation (serum MDA levels), biological indicator of antioxidant defense (serum SOD enzyme activity values), and physiological marker of cellular longevity (telomerase activity) will be reported using the mean change from baseline to postintervention (along with the SD and 95% CIs) calculated for the study group. In addition to these mean changes, the proportion of participants experiencing any incidental rescue events (such as the percentage of volunteers) will be tracked descriptively as feasibility and safety outcomes.

### Data Collection Form Accessibility

This protocol covers an ongoing exploratory trial with data collection currently in progress; the data logging layout is fully integrated within the study’s clinical CRF. This form includes dedicated fields for tracking participant alphanumeric codes, specimen collection time stamps, and laboratory assay results (MDA, T-SOD, and telomerase concentrations). The blank data collection templates within the CRF framework are securely archived and can be provided by the corresponding author to reviewers or editors upon reasonable academic requests.

### Participant Retention and Discontinuation Protocols

Participant retention is optimized through the fully managed inpatient environment. This trial tracks an existing clinical service where healthy volunteers are admitted as full hospital inpatients for the duration of the *Śodhana* therapy; therefore, typical outpatient compliance barriers like travel issues, appointments being forgotten, or accidental dietary deviations are naturally eliminated.

For participants who voluntarily withdraw or deviate from the intervention protocols after formal enrollment, active procedures are immediately halted to protect participant autonomy and safety. Unless written consent is completely revoked, the specific outcome data collected and retained for these individuals will consist of baseline serum MDA, T-SOD, and telomerase levels, along with a documented record of the exact chronological point and clinical reason for the protocol deviation or study exit. The reasons for nonadherence and nonretention will be recorded on the CRF. All recorded reasons will be compiled into a standardized trial flow diagram and fully disclosed in the final manuscript publication.

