#### Handling of Intercurrent Events

Intercurrent events anticipated in this protocol include clinical dropout, voluntary withdrawal, or protocol nonadherence (such as violating the inpatient *Ahara* or *Vihara* constraints). To handle these events, a “While-On-Treatment” strategy will be used. The target estimation focuses strictly on the biological treatment effect achieved while participants successfully adhere to the intensive inpatient intervention. Data points collected up to the exact moment of any protocol violation or withdrawal will be retained, while missing postevent endpoints will be mathematically handled using multiple imputation methods within our multivariable regression models, preventing bias from complete-case attrition.

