### Statistical Handling of Missing Data

This trial evaluates objective biochemical endpoints within a strictly monitored hospital inpatient setting; the incidence of missing data is anticipated to be extremely low (<5%). Any missing data points are assumed to follow a missing completely at random mechanism, as data omissions would stem strictly from random logistical or laboratory anomalies.

Missing data will be handled using an available case analysis (pairwise deletion) framework for the primary longitudinal comparisons, ensuring that all available valid pairs of pre- and postintervention biochemical metrics are fully utilized without fabricating data. To verify that this approach does not introduce statistical bias, a conservative baseline observation carried forward (BOCF) sensitivity analysis will be executed concurrently. Under the BOCF framework, any missing postintervention value will be replaced by the participant’s own baseline value, assuming zero therapeutic change. This dual-validation approach guarantees a highly transparent, noninflationary evaluation of the trial’s biochemical endpoints.

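### The discontinuation rule contradicts the reason given for missing completely at random, and agreement of the available-case and BOCF P values cannot show that attrition bias is absent

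*Protocol article*

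**What the plan says.** Five parts of the protocol article bear on this.

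- **Participant Retention and Discontinuation Protocols.** Procedures stop at once for a participant who withdraws or deviates. Unless consent is fully revoked, "the specific outcome data collected and retained for these individuals will consist of baseline serum MDA, T-SOD, and telomerase levels", together with when and why the participant left.
- **Abstract, Methods.** There are two measurement times: the markers including "telomerase activity will be measured on day 0 and on the next day following completion of the" graduated diet (day 18 to 20). No marker is measured in between.
- **Statistical Handling of Missing Data.** Losses are expected to stay below 5% and are taken as MCAR, because "data omissions would stem strictly from random logistical or laboratory anomalies". The primary method is fixed: "Missing data will be handled using an available case analysis (pairwise deletion) framework for the primary longitudinal comparisons". The abstract repeats the MCAR assumption.
- **Sensitivity Analyses.** A missing post-intervention value, or one affected by a protocol deviation, is replaced by the participant's baseline. If both analyses fall on the same side of P = .05, the findings are to be regarded as stable and clear of attrition bias.
- **Handling of Intercurrent Events.** Dropout, withdrawal and nonadherence are anticipated, and a while-on-treatment strategy is named. "Data points collected up to the exact moment of any protocol violation or withdrawal will be retained", and "missing postevent endpoints will be mathematically handled using multiple imputation methods within our multivariable regression models", with the stated aim of avoiding bias from complete-case attrition. Statistical Measures gives those regression models a secondary place: "secondary multivariable analyses will be introduced to evaluate the influence of potential baseline confounders".

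**The concern.** The discontinuation rule makes T1 missing as a direct consequence of withdrawal or deviation, with a clinical reason recorded. The missing-data section says that such omissions arise only from chance faults in logistics or the laboratory. Both statements cannot describe the same trial.

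The estimand does not close the gap. With only two time points, a participant who stops has no on-treatment value after baseline, so a while-on-treatment strategy has nothing to use. The multiple imputation offered instead sits in secondary models, and the primary comparison uses the complete pairs that the estimand section says it wants to avoid relying on. With no T1 from any stopper, imputation can only borrow from completers.

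What is at stake is a published robustness statement. If the BOCF check passes whatever happened to those who left, a reader would be told that attrition bias has been excluded when it has not been examined.

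**Working it through.** **Inputs from the document.** N = 53, a 20% dropout allowance and paired d = 0.395 at 80% power (Sample Size); missing data below 5% (Statistical Handling of Missing Data); BOCF and the P < .05 agreement rule (Sensitivity Analyses).

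**The plan's own figures.** 1.96² × 0.25 / 0.15² = 42.68, and 42.68 / 0.80 = 53.4, which agrees with 53. A two-sided paired t test with n = 53 and d = 0.395 has power 0.806, which agrees with 80%.

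**Number of stoppers, if 53 are enrolled.** 0.05 × 53 = 2.65, about 3, leaving n = 50. 0.20 × 53 = 10.6, about 11, leaving n = 42.

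**Why P barely moves.** Let S be the sum of the changes, Q the sum of their squares, and r = S²/Q. For N values, t² = r(N − 1)/(N − r). BOCF adds k zeros: S, Q and hence r stay the same, and only N rises from n to n + k. From the completers' t, r = t²n/(n − 1 + t²).

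| n completers | k missing | t, available-case → BOCF | P, available-case → BOCF |
|---|---|---|---|
| 50 | 3 | 2.010 → 2.006 | .0500 → .0501 |
| 50 | 3 | 2.680 → 2.670 | .0100 → .0101 |
| 42 | 11 | 2.020 → 2.004 | .0500 → .0503 |
| 42 | 11 | 2.701 → 2.659 | .0100 → .0104 |

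First row: r = 2.0096² × 50 / (49 + 2.0096²) = 3.807, and t² = 3.807 × 52 / (53 − 3.807) = 4.024, so t = 2.006.

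Significance is lost only if the available-case P lies between about .0499 and .0500 (k = 3) or between about .0497 and .0500 (k = 11). In 200,000 simulated trials with normal changes and completers' d = 0.395, the verdicts differed in about 0.02% (k = 3) and just under 0.1% (k = 11). If 53 complete and 13 more stop, the figure is about 0.05%. A Wilcoxon signed-rank test that discards zero differences gives identical P values.

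**Does agreement indicate absence of bias?** Assume a true mean change of zero in all 53 enrolled, with stoppers 1 SD worse than completers. With 20% missing, the mean change is +0.20 SD in available cases and +0.16 SD under BOCF, and both analyses are significant in the favourable direction in 24.4% of trials, against a nominal 2.5%. With 5% missing the figure is 5.2%. The verdicts agreed in at least 99.9% of trials in every setting, biased or not.

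**Size of the shift in the estimate.** If stoppers gain nothing, the available-case mean exceeds the all-starters mean by 53/50 = 1.06 with 3 stoppers, or 53/42 = 1.26 with 11. At d = 0.395 and 3 stoppers, 0.395 × 50/53 = 0.373. The shift of 0.022 SD compares with a standard error of 1/√50 = 0.14 SD.

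**Comparing BOCF and available-case means instead.** Where T1 is missing, the BOCF mean is always n/(n + k) times the available-case mean. That comparison returns the dropout fraction and says nothing about the stoppers.

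**The case against.** **The check can move on another reading.** Sensitivity Analyses also sets protocol-deviated values to baseline, which may imply that some deviators have a T1. Such values would enter the available-case analysis and be zeroed under BOCF. At d = 0.395 the verdicts would then differ in about 6% of trials with 3 deviators and about 15% with 11. This stands as a limit: the near-automatic pass applies to missing T1. A reader might infer that the check can never fail, and the text does not support that. But the discontinuation section says a deviator's later value is not kept, so the two sections need reconciling.

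**Event-driven loss does not disprove MCAR.** Correct. A reader might infer that the data are shown not to be MCAR. The document shows only that the reason given for MCAR is wrong. Missing at random given baseline also remains possible. Exit reasons will be recorded and published, which helps readers judge.

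**The declared target is close to an effect in adherers.** Largely right. The estimand focuses on the effect while participants adhere, so the all-starters comparison is an illustration against a target the protocol does not declare. A completer effect is acceptable if it is called that.

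**The trial is exploratory, and under 5% loss matters little.** This holds for the estimate. It does not rescue the inference, which is invalid at any loss rate. The protocol also plans to use the effect sizes in designing a later randomised trial.

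**Enrolment may exceed 53.** Expected Completion ends the trial once 53 have completed, so the denominators above may be slightly off. The conclusion does not change.

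**Conclusion.** The point holds in limited form. The discontinuation rule contradicts the stated reason for MCAR. Where T1 is missing, agreement between the available-case and BOCF P values is close to guaranteed (verdicts differ in roughly 0.02% to 0.1% of trials), so it cannot support a claim that attrition bias is absent. The estimand section and the missing-data section also name different handling.

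A reader might go further and infer that the primary estimate is materially biased. The documents do not show this. At the expected loss of under 5% the illustrated shift is about 6% of the effect, well inside sampling error. It reaches about 25% only if the 20% allowance is realised and stoppers gain nothing.

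The t-test algebra is exact. The discordance rates assume normal changes and d = 0.395. The false-positive rates rest on an assumed 1 SD difference between stoppers and completers, for which the protocol gives no figure.

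**What to change.** Data analysis is reported as pending, so these changes can still be prespecified.

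1. **Abstract and Statistical Handling of Missing Data:** delete the statement that omissions are purely random, and the unqualified MCAR assumption.
2. **Handling of Intercurrent Events and Statistical Handling of Missing Data:** state that available-case analysis is primary and describes an effect in completers, and that multiple imputation is secondary.
3. **Sensitivity Analyses:** delete the rule that equates P-value agreement with absence of attrition bias. Replace it with a delta-adjusted or tipping-point analysis of the mean change with its 95% CI. Assign those without T1 a range of assumed changes, including worsening, with BOCF (zero change) as one point in that range. For example, with 42 completers at 0.395 SD and 11 stoppers assigned −0.5 SD, the mean is (42 × 0.395 − 11 × 0.5)/53 = 0.21 SD, against 0.31 SD under BOCF.
4. **Sensitivity Analyses and Participant Retention:** say whether a deviator can have a T1 value and, if so, whether it is kept.

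Exit blood samples are optional and not needed for this correction. They would be few, early samples would not be comparable with day 18 to 20 values, and they could no longer cover stoppers among the first 27 participants.

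The cost is wording, a little more analysis and a less favourable robustness statement.
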